## 3. Methodology and data analysis

### 3.1 Cognition and neuroimaging investigations

#### 3.1.1 NIH-toolbox cognitive battery and emotional battery

Comprehensive neuropsychological testing is the gold standard for diagnosis of MCI, consisting of hours of testing to evaluate specific cognitive domains that can help identify the etiology of impairment, as well as socioeconomic and demographic factors that may contribute to cognitive decline [46]. Therefore, NIH-toolbox Cognitive Battery and select questionnaires from NIH-toolbox Emotion Battery will be implemented to assess categories of crystalized intelligence (dependent upon past learning experience), fluid abilities (domains of executive function, attention, episodic, memory, visual learning, processing speed, and working memory) and affective function. Total duration of both Cognitive and Emotion Battery is ~45 minutes and is administered at visit one and 18-month follow-up. The NIH Toolbox is a sensitive approach to evaluate age-related changes in cognitive performance, mild cognitive impairment and dementia [47], and is suitable for clinical studies with repeating measures of 4-week interval or longer [48,49]. All neurocognitive assessment will be done under supervision of a clinical neuropsychologist in the Department of Psychiatry and Behavioral Sciences at the OUHSC.

Fully adjusted scale score (mean = 50; SD = 10), which compares the score of the participant to nationally representative normative sample of NIH tool box test takers, accounting for age, sex, race, and education will be used for analysis of specific cognitive domains (picture vocabulary test, flanker inhibitory control and attention test, list sorting working memory test, dimensional change card sort test, pattern comparison processing speed test, picture sequence memory test, oral reading recognition test), and composite scores (fluid composite, crystallized composite, total composite, early childhood composite). Raw score will be used for oral symbol digit test (number of correct responses in two minutes) and unadjusted scale score (mean = 100; SD = 15) representative of normative sample without correction for other demographic variables will be used for all questionnaires within the Emotional Battery (emotional support, friendship, loneliness, perceived hostility, perceived rejection).

#### 3.1.2 Neuroimaging investigations

Prior to visit one, patients were diagnosed with MCI and neuroradiologically (i.e., MRI) assessed for small vessel complications. In a recent meta-analysis from Guo and Shi, small vessel ischemic damage to the brain, evidenced by white matter hyperintensities (WMH) on MRI, was associated with increased risk of development of MCI and dementia [50]. Ischemia localized to, and originating from small vessels, and microbleeds are two common pathologies in cerebral small vessel disease (CSVD) [51], and can be imaged by MRI through T2 fluid attenuated inversion recovery (FLAIR) and T2* gradient echo (GRE) or susceptibility weighted imaging sequences (SWI), respectively. All study participants, in addition to the first MRI scan performed as a point of care before enrollment into the study, will be neuroradiologically evaluated at Visit 2 using a 3T MRI. Increased burden of WMH (i.e., confluence of deep foci and extension of periventricular WMH into the deep white matter) are one of the most common manifestations on T2 FLAIR MRI imaging for diagnosis of CSVD [52] and is associated with acute and recovered COVID-19 patients [22]. Moreover, burden of WMH, determined by Fazekas scale [53], will be longitudinally assessed as a contributing factor for conversion of MCI to dementia in COVID-19 patients. The Fazekas scale grades the periventricular and deep white matter from 0–3, depending on the size and confluence of the lesions [53,54]. This grading system is the most widely used system to date to identify severity of white matter pathology [53,55]. Additionally, presence of microbleeds will be neuroradiologically assessed, as this pathology is also associated with COVID-19 and has a specific pattern of distribution that distinguishes CSVD burden in recovered and acute COVID-19 patients from other known causes (i.e., hypertension, acute respiratory distress syndrome) [22].

WMH burden will be evaluated at baseline by Fazekas scale to determine if there are differences at diagnosis that could influence results at cross-sectional cognitive and physiological measurements. Longitudinally, WMH burden will be calculated at 18-months to determine the influence of WMH on progression to dementia and whether COVID-19 increases burden of WMH in patients with MCI.

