## 2. Study aims and protocol

### 2.1 Study aims

To determine whether history of COVID-19 infection in patients with MCI disrupts systemic endothelial function and impairs NVC response compared to MCI patients with no history of COVID-19 infection.To determine whether history of COVID-19 infection aggravates the impairment of fluid cognitive abilities in patients with MCI.To determine whether impairment of NVC responses in recovered COVID-19 patients with MCI contributes to increased conversion of MCI to dementia.To determine whether COVID-19 related increases in white matter hyperintensity (WMH) burden contribute to conversion of MCI to dementia.

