### 2.9 Study variables

All variables included in the study are represented in **Table 1**, and separated based on level of measurement (continuous, ordinal, discrete, binary). Below, the variables are described for each specific aim, as mentioned in the *Study aims* section.

**Table 1 pone.0289508.t001:** Summary of variables for study aims.

Variable	Method of Measurement	Operational definition	Level of measurement
**NVC**	fNIRS	Change in relative HbO concentration in cortical small vessels during cognitive task	Continuous
**Band-limited power**	EEG	Amount of electrocortical activity in distinct frequency bands during cognitive task	Continuous
**Retinal arteriolar function**	DVA	Retinal arteriolar response to flickering light stimulus (NVC stimulus)	Continuous
**Microvascular endothelial function**	LSCI	Small vessel hand perfusion following the release of 5-minute occlusion	Continuous
**Macrovascular endothelial function**	FMD	Percent change in brachial artery diameter from baseline to release of 5-minute occlusion	Continuous
**Pro-inflammatory cytokine levels**	Magnetic bead-based multiplex assay	Quantified fluorescence intensity in pro-inflammatory cytokine levels	Continuous
**Endothelial dysfunction biomarkers**	Magnetic bead-based multiplex assay	Quantified fluorescence intensity in cardiovascular disease panel markers	Continuous
**Antioxidant capacity**	HORAC activity assay	Fluorescence decay curve: time until complete decay of fluorescent probe	Continuous
**Fluid intelligence**	NIH Toolbox	Individual and categorical T score based on cognitive test responses	Continuous
**Crystalized Intelligence**	NIH Toolbox	Individual and categorical T score based on cognitive test responses	Continuous
**Emotion Score**	NIH-Toolbox	Individual T-score based on normative population data	Continuous
***n*-back working memory performance**	n-back	Percentage of correct responses and reaction time during *n*-back blocks	Continuous
**Blood pressure**	AD instruments	Blood pressure recorded during visits	Continuous
**Time since SARS-CoV-2 Infection**	Demographic	Duration from COVID-19 diagnosis to Visit 1	Continuous
**Age**	Demographic	Age (in years) of participants at each visit	Discrete
**Fazekas scale**	MRI	WMH burden (0–3) periventricular and deep	Discrete
**MoCA**	Demographic	Montreal cognitive assessment score (0–30)	Discrete
**ACE score**	ACE questionnaire	Adverse childhood experience questionnaire, scored 1–10 with a score of 10 having high ACE	Discrete

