■ Aim 1 variables will be used to address whether history of SARS-CoV-2 infection impairs systemic endothelial function and NVC response in patients with MCI. Variables included in this Aim are: NVC, band-limited power of brain waves, retinal arteriolar function, microvascular endothelial function, macrovascular endothelial function, endothelial dysfunction biomarkers, pro-inflammatory cytokine level, antioxidant capacity, COVID-19 status, SARS-CoV-2 variants, time since infection, and vaccination history.■ Aim 2 variables will be used to address whether MCI patients with history of COVID-19 have impaired fluid cognitive function compared to MCI patients with no COVID-19 history. Variables included in this Aim are: *n*-back working memory performance, fluid intelligence, COVID-19 status, SARS-CoV-2 variants, time since infection, and vaccination history.■ Aim 3 variables will be used to address whether history of COVID-19 in patients with previously diagnosed MCI contributes to progression to dementia, and whether impaired NVC associates with increased progression to dementia. Variables included in this Aim are: NVC, retinal arteriolar function, band limited power of brain waves, COVID-19 status, SARS-CoV-2 variants, time since infection, vaccination history, and progression of MCI to dementia.■ Aim 4 variables will be used to address whether history of COVID-19 in MCI contributes to increased burden of WMH, and whether elevated level of WMH burden contributes to increased progression of MCI to dementia. Variables included in this Aim are: Fazekas scale, COVID-19 status, SARS-CoV-2 variants, time since infection, vaccination history, and progression of MCI to dementia.

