### 4.2 Longitudinal data analysis

Continuous data will be analyzed by 2-way ANOVA and categorical with Chi-square or Fisher’s exact test for within and between groups (COVID+ vs COVID-) comparison. Effect size will be calculated for all within and between group analyses. For **primary outcome** analysis, we will determine whether COVID-19 related impairment in NVC and increases in WMH burden contributes to progression to dementia. Progression to dementia within and between groups will be analyzed and multivariate analysis will be conducted to determine the effect of COVID-19, NVC (i.e., fNIRS), change in WMH burden, and interaction between group (COVID+, COVID-) and NVC and WMH burden on progression to dementia. **Secondary outcome** measures (i.e., FMD, LSCI, EEG, DVA, NIH Toolbox, circulating factors) will be compared within and between groups. Demographic variables, COVID-19 variants, duration of COVID-19 and vaccination will be assessed as factors for progression to dementia through logistic regression. **Exploratory analyses** will include univariate analysis of all demographics, physiologic, cognitive, and structural variables, and their effect on progression to dementia. All values with a p value <0.2 will be included in a multivariate model to assess their contribution to progression to dementia. We expect that several variables will have p value <0.2; therefore, we will conduct dimensionality reduction before adding into the model to assess variables which have strongest correlation with principal components. The limitation for the multivariate model will be sample size, however this is not a primary outcome measure and is used to generate new hypotheses to test in future studies.

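### The WMH predictor of dementia is worded as a change in some sections and as a level in others, including within the section 4.2 model; section 4.2 should use change throughout, with baseline Fazekas grade as a covariate

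*Protocol article*

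**What the plan says.** All references are to the protocol article.

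- **Section 2.1, Aim 4** asks about an increase: "To determine whether COVID-19 related increases in white matter hyperintensity (WMH) burden contribute to conversion of MCI to dementia".
- **Section 2.9, Aim 4 variables** asks about a level: "whether elevated level of WMH burden contributes to increased progression of MCI to dementia". The list names only the Fazekas scale.
- **Table 1** defines the variable as "WMH burden (0–3) periventricular and deep". It has no row for change.
- **Section 3.1.2** says that WMH burden "will be longitudinally assessed as a contributing factor for conversion of MCI to dementia in COVID-19 patients", and later: "Longitudinally, WMH burden will be calculated at 18-months to determine the influence of WMH on progression to dementia". That sentence goes on to ask whether COVID-19 raises WMH burden. The baseline grade has its own stated purpose: "WMH burden will be evaluated at baseline by Fazekas scale to determine if there are differences at diagnosis" that could affect the cross-sectional measurements.
- **Section 4.2, primary longitudinal analysis**: "multivariate analysis will be conducted to determine the effect of COVID-19, NVC (i.e., fNIRS), change in WMH burden, and interaction between group". The interaction is then between group and both NVC and WMH burden, without the word change.
- **Section 2.7** places the baseline WMH assessment at MCI diagnosis, before the pandemic, and the second at 18 months.

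No section says which wording governs, and none names baseline WMH as a covariate in the primary dementia model.

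**The concern.** Level and change are different predictors. A patient with Fazekas grade 3 on both scans has the highest possible level and zero change. A patient who moves from grade 0 to grade 1 has a low level and a positive change.

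The month-18 level contains everything that was on the pre-pandemic scan, and that part cannot be due to COVID-19. Section 3.1.2 itself cites a meta-analysis linking WMH to the risk of dementia. A level term can therefore be positive because of long-standing disease alone, while Aim 4 asks about COVID-related increase. The reverse can also happen: a real effect of new WMH can be diluted by stable old WMH.

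This bears on the WMH half of the primary outcome. The group interaction matters most, because it is the WMH term closest to the COVID-specific hypothesis and the one where 4.2 drops the word change.

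**Working it through.** The article gives no figure for this point, so the check is of wording first and consequence second.

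**1. Wording side by side**

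| Place | WMH term set against dementia |
|---|---|
| 2.1, Aim 4 | increase |
| 4.2, main effect | change |
| 4.2, group interaction | burden, no mention of change |
| 2.9, Aim 4 variables | elevated level |
| Table 1 | grade 0–3, no change variable |
| 3.1.2 | burden at 18 months; also described as assessed longitudinally |

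Two places say change. Section 2.9 says level. Section 3.1.2 and the 4.2 interaction are open to either reading.

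**2. The interaction read literally**

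Let B be baseline grade, C the change, L = B + C the month-18 level, and G = 1 for COVID-19 history. Leaving out the NVC terms, 4.2 read literally is

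logit(p) = a + g·G + c·C + h·G·L,

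with no main effect of L. Suppose that in truth logit(p) = a + b·B in both groups, so that change does nothing and COVID-19 modifies nothing. For G = 1 the WMH part of the model is c·C + h·(B + C) = h·B + (c + h)·C. The baseline effect b can enter only through h, so h is pulled towards b although the true interaction is zero. If a main effect of L were added, h would be the difference in slope between the groups, which is zero here. The harm through the interaction thus depends on how the model is completed.

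**3. Size if the level is used alone (illustrative)**

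Inputs from section 2.4: up to 200 patients, and conversion (10 + 23)/(18 + 100) = 33/118 = 28%. Assumed: 12% loss, so 200 × 0.88 = 176; baseline Fazekas 0/1/2/3 in 25/35/25/15%; 20% of those below grade 3 gain one grade; one score per patient. Logistic regression, two-sided 0.05, 3,000 replicates per setting. Level and change correlate 0.23.

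| True odds ratio per grade | Level significant | Change significant | Change adjusted for baseline |
|---|---|---|---|
| Baseline 1.3, change 1 | 31% | 4% | 4% |
| Baseline 1.5, change 1 | 61% | 4% | 4% |
| Baseline 1.8, change 1 | 92% | 7% | 5% |
| Baseline 1, change 3 | 9% | 76% | 75% |
| Baseline 1.5, change 3 | 78% | 60% | 73% |

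In the first three rows change has no effect, so every significant result is false as an answer about increase. In the last row the 78% for the level comes largely from baseline WMH.

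**4. Sensitivity to the assumptions**

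A second set used 200 × 0.90 = 180 patients, half with COVID-19 history, about 39% dementia, baseline shares 20/40/25/15%, and one-grade increases in 15% or 30% plus 10 points with COVID-19. COVID-19 status was in the model. With no effect of change, the level was significant in 29–34%, 67–68% and 94–98% of studies for baseline odds ratios 1.3, 1.5 and 2.0. Unadjusted change gave about 6%, 6–8% and 9–12%; the excess arises because grade 3 cannot rise, which ties change to baseline. Adjusted change gave 4–5%. With no baseline effect, all versions stayed at 3–6%.

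**The case against.** The strongest reply is that section 4.2 is the only place that specifies the primary longitudinal model, and that its main effect is change. Aim 4 and the abstract agree. Section 3.1.2 is a measurement section. Its sentence also asks whether COVID-19 increases burden, which needs both scans, so it may say only when the second reading is made. In section 2.9, the elevated level follows directly on a clause about increased burden and may refer back to it.

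Most of this stands. A reader might infer that the protocol commits the primary dementia model to the month-18 level and so carries a 31–92% false-positive rate. The article does not support that: 4.2 names change for the main effect, for which the first simulation gives 4–7%. A reader might also take the simulation to show a false COVID-19 effect. It shows only a false WMH association. The first set has no COVID-19 group, and the second has COVID-19 as a main effect but no interaction. Neither includes NVC or the separate periventricular and deep grades.

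The reply does not remove the conflict. Section 2.9 states the Aim 4 question itself as one about level, and 4.2 cannot settle the matter because it drops the word change in its own interaction.

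On baseline adjustment, it is fair to say that covariate detail is often left to a fuller document, and that adjustment changes little in several settings (76% against 75% power). It is part of the repair to the change term, not a separate omission.

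**Conclusion.** The inconsistency is real, and its consequence is conditional. The WMH term is a change in Aim 4 and in the 4.2 main effect, a level in 2.9, and undetermined in 3.1.2 and in the 4.2 interaction. If change is used throughout, pre-existing WMH does little damage. If the level is used in the interaction or for Aim 4, disease already present before the pandemic can be reported as COVID-related increase contributing to conversion.

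The simulated rates show direction, not expected size: the Fazekas distribution, the rate of grade increase and the odds ratios are all assumed. The direction was the same under both sets of assumptions, and it vanishes when baseline WMH does not predict dementia.

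Adjusting for baseline keeps the false-positive rate at about 4–5%. When baseline and change both predict dementia, it raises power from 60% to 73% in the setting above; repeat runs gave 51–56% rising to 70–72%. This should be corrected, but it does not invalidate the planned analysis.

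**What to change.** - **Section 4.2:** define the WMH term as change in Fazekas grade from the diagnostic scan to month 18. Use it for both the main effect and the group interaction, and add baseline Fazekas grade as a covariate in the same model.
- **Section 2.9:** reword the Aim 4 question as one about increase in WMH burden.
- **Table 1:** add change in Fazekas grade as a variable.
- **Section 3.1.2:** state that the month-18 grade is read in order to calculate the change, and that the baseline grade also serves the dementia analysis.
- Keep the month-18 level as a descriptive or sensitivity result, labelled as such.

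The cost is wording in four places and one extra model term. Both scans are already planned and the baseline grade is already collected. The change should be made before follow-up ends, which section 3.7 expects in 2026.

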### 3.2 Physiological investigations

#### 3.2.1 Blood pressure measurement

Blood pressure (BP) is measured in accordance with the 2017 AHA/ACC Hypertension Guideline for Standard Measurement of BP [56]. Recordings are taken several times during each ~four-hour visit, before cognitive testing, before FMD, and before LSCI. Uncontrolled hypertension is known to cause deleterious effects to the endothelium and systemic vasculature [57]. Hence, patients with uncontrolled hypertension are excluded, in brief, due to known impairments of cerebral autoregulation [58], risk of cerebrovascular complications [59], and dysregulation of the macro- and microvasculature [60].

Systolic, diastolic, and mean arterial pressure will be calculated from patient blood pressure recordings and compared between groups (COVID-19+ and COVID-19-) to assess for differences, which may influence vascular physiological measurements.

#### 3.2.2 Functional near-infrared spectroscopy (fNIRS) and n-back paradigm

We are using fNIRS to evaluate NVC in a real-time, continuous measure, during blocks of increasing cognitive workload (*n*-back). The cognitive *n*-back is a working memory paradigm used to evoke NVC responses. Patients are seated in-front of a 22” monitor that displays the task, while they rest their right hand on the mouse. Before the measurement, patients are instructed to perform to the best of their ability and are walked through each *n*-back ‘block’ to ensure understanding of the paradigm. Thirty-two letters are presented in a randomized sequence during each block by the ePrime 3 software (Psychology Software Tools, Sharpsburg, PA) [28]. Each letter is displayed on the screen for 250 ms followed by a random time interval pause (1950±100 ms) before the appearance of the next letter. Patients are instructed to provide a correct response by click the left mouse button only when they identify a target stimulus, which depends on the type of the task for a given block. Below are the three tasks the patients are presented with:

0-back: identification of and response to the letter ‘**W**’. The 0-back is the first and third block of the *n*-back paradigm, with each block being a different sequence of letters with the ‘**W**’ stimulus in a randomized order.1-back: identification and response to repeated letters in a sequence (e.g., Y-M-S-**S**). The target stimulus is the second letter in the sequence.2-back: identification of a pattern where every other letter is repeated (e.g., Y-M-**Y**-S). The response is correct if the patient clicks the left mouse button when they recognize a letter that is the same from two positions back.

The length of each block is 72 seconds with ten second intervals between them and are administered as follows: 0-back→ 1-back→ 0-back→ 2-back.

During the *n*-back paradigm, patients wear a 128 port Easycap head cap (Easycap GmbH, Woerthsee-Etterschlag, Germany) suited with 16 sources and 16 detectors (NIRx Medical Technologies LLC, Glen Head, NY) to measure continuous changes in oxy- (HbO) and deoxy-hemoglobin (HbR) concentration. Hemodynamic responses are recorded from 48 channels (source-detector pairs) according to the international 10–20 system at a sampling frequency of 3.9 Hz and measurements are performed in a quiet, dark room. The light sources are in the NIR range, emitting light that can readily penetrate superficial layers of the scalp and skull to enter the cerebral cortex [61]. NIR wavelengths used for in vivo optical imaging are 760 nm and 850 nm, each specifically optimized for calculating HbR and HbO relative concentration changes, respectively. HbR and HbO are chromophores and based on attenuation of the NIR light at detectors, changes in hemoglobin concentration can be measured according to the continuous-wave principle [40]. These measures are limited to the cerebral cortex, a depth of 1.5 cm [62], and are standardized topographically by separating the distance between sources and detectors at 3 cm, allowing for a predictable ‘banana’ shaped path between optodes [63]. However, due to biological membranes and lipid bilayers, there is significant scattering of light in biological tissues [64]; hence, absorption changes in HbO and HbR can only be measured by the applied continuous-wave technique if constant scattering loss is assumed. To account for this, the Beer-Lambert Law (i.e., absorbance proportional to path-length and the concentration of chromophores) is modified for a highly scattering medium [65,66]. In addition to the 3 cm separated sources and detectors, channels with a smaller distance between sources and detectors (8 mm) are added to account for shallower hemodynamic changes in extracerebral structures (e.g., skin, skull), allowing for removal of extracerebral hemodynamic fluctuations [40,67]. Measurement of NVC using fNIRS is validated by functional magnetic resonance imaging (fMRI) [68] studies and is sensitive to changes in cognitive function in aging [40] and age-related diseases [42]. Additionally, decreases in HbO measured by fNIRS have been reported in mild cognitive impairment [69] and dementia [70].

fNIRS data processing and analysis will be implemented in Matlab 2022a (Mathworks, Natick, MA, USA) using custom scripts written by PM, implemented in a pipeline created by the Brain AnalyzIR toolbox (commit 46c645d) [71]. Before analysis, preprocessing steps will be applied to remove artifacts not originating from brain activation by low-pass filtering (0.02–0.4 Hz). Further, once optical densities of brain regions are transformed into hemodynamic signals by the modified Beer-Lambert law, obtained relative HbO concentrations will be pre-whitened, attenuating correlated effects due to systemic physiology and motion. Slow drifts will then be eliminated using discrete cosine transform-based high-pass filter (0.009 Hz). Scalp hemodynamic changes, captured by short channel source-detector pairs, will be subtracted from the remaining channels.

Cognitive performance during the *n*-back test will be calculated as percentage of correct responses and reaction time for each patient during each *n*-back block (0-back, 1-back, 2-back).

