### 2.2 Study design

This study will test the hypothesis that COVID-19 infection promotes systemic endothelial dysfunction, impairing NVC responses and promoting white matter damage, contributing to the progression of MCI to dementia. To test this hypothesis, we will prospectively follow patients, who are diagnosed with MCI, with or without history of SARS-CoV-2 infection, for 18 months. The timeline for study design and investigative measurements are represented in **Fig 1.** Study participants will be evaluated for eligibility and enrolled through neurology clinics at the University of Oklahoma Health Sciences Center (OUHSC) and Oklahoma City Veterans Affairs (VA) Medical Center (Visit 0). Upon enrollment, patient history, demographic data, standard risk factors for dementia, cognitive status and WMH status (MRI scan) will be recorded. Blood collection, cognitive tests (NIH-toolbox, *n-*back), and baseline physiologic assessments for peripheral endothelial function (flow-mediated dilation [FMD], laser speckle contrast imaging [LSCI]) and NVC responses (functional near-infrared spectroscopy [fNIRS], dynamic retinal vessel analysis [DVA]) will be conducted at the OUHSC Translational Geroscience Laboratory (Visit 1). Study participants will undergo semi-annual clinical neurologic evaluations as a part of standard care. In addition to COVID-19 status since enrollment (e.g., PCR+/-, symptoms), progression from MCI to dementia will be assessed by the clinical neurology team with final adjudication made through consensus management conferences. Repeat of all physiological assessments, cognitive tests, and serum collection will be performed at month 18 (Visit 2), and the second MRI scan will be performed. If some participants decide to terminate their participation in the study for any reason, they will be invited to an early termination visit, which will include the same evaluations as in Visit 2.

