## 4. Statistical analysis

### 4.1 Cross-sectional data analysis

Upon testing for normality of continuous data, independent t-test or Mann-Whitney *U* Test will be used for group comparison (COVID+ vs COVID-) and Chi-square or Fisher’s exact test for group comparison of categorical variables. Effect size will be calculated for all within and between group analyses. For **primary outcome** analysis, testing whether COVID-19 impairs NVC responses in MCI patients, fNIRS data will be analyzed using a pipeline based on General Linear Model (GLM) approach created using the Brain AnalyzIR toolbox. At the first (subject) level, regression (β) coefficients characterize NVC response and will be estimated for channels of interest in the prefrontal cortex across all n-back blocks and chromophores (HbO and HbR). At the second (group) level the GLM treats COVID status as an independent categorical factor, while the n-back block as a repeated measures factor and yields corresponding *t*-contrasts comparing NVC response within and between groups. We will test whether demographic variables, COVID-19 variants, duration of COVID-19 and vaccination influences the primary outcome through linear regression. Moreover, we will create a multivariate model using β coefficients, generated from the fNIRS pipeline, to determine whether COVID-19 predicts impairment in NVC in MCI patients. Univariate analyses of factors that may contribute to NVC impairment (i.e., age, sex, baseline structural MRI abnormalities) will be conducted, and analyses with a p value of <0.2 will be included in the multivariate model. **Secondary outcome** measures (i.e., FMD, LSCI, EEG, DVA, NIH Toolbox, circulating factors) will be compared between groups. Additionally, we will determine whether history of COVID-19 contributes to impairment in functional cognitive measures (i.e., n-back, NIH Toolbox) by multiple and simple linear regression. For **exploratory analyses**, we will determine whether group (COVID+ vs COVID-) alters the relation between NVC and peripheral, cognitive, and structural measures through multiple regression. Correlations for these variables will be performed within groups to determine strength of relationship with NVC.

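### The fNIRS scalp correction is described as a subtraction with no fitted weight; read literally, it leaves scalp signal in the primary NVC measure and could bias the COVID contrast in either direction

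*Protocol article*

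**What the plan says.** Section 3.2.2 describes two kinds of fNIRS channel. The measuring channels are "standardized topographically by separating the distance between sources and detectors at 3 cm". In addition, "channels with a smaller distance between sources and detectors (8 mm) are added to account for shallower hemodynamic changes in extracerebral structures", with the stated purpose of "allowing for removal of extracerebral hemodynamic fluctuations".

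The processing paragraph of the same section specifies filter cut-offs, pre-whitening and a fixed toolbox commit. On the scalp signal it says only: "Scalp hemodynamic changes, captured by short channel source-detector pairs, will be subtracted from the remaining channels". No weight, fitted coefficient or regression is mentioned.

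Section 4.1 then defines the primary NVC measure: "regression (β) coefficients characterize NVC response and will be estimated for channels of interest in the prefrontal cortex". No short-channel term is named in that first-level model. The betas go into the COVID comparison: "At the second (group) level the GLM treats COVID status as an independent categorical factor". Section 4.2 uses fNIRS NVC again as a predictor in the primary model for progression to dementia.

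**The concern.** A detector 8 mm from its source and one 3 cm away do not see the scalp over the same path. Section 3.2.2 itself stresses path length and scattering when it explains the modified Beer-Lambert law. The scalp signal in a long channel is therefore some multiple k of that in the short channel. Plain subtraction assumes k = 1 in every channel and every patient. Where k differs from 1, part of the scalp response stays in the beta that is called NVC.

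This matters more here than in most fNIRS studies because of the exposure. Section 2.2 hypothesises that "COVID-19 infection promotes systemic endothelial dysfunction, impairing NVC responses and promoting white matter damage", and section 3.2.6 measures skin microvascular function as one expression of that. If skin vessels respond differently after COVID-19, the scalp response to the task might differ by group as well. Any residue would then enter the COVID contrast, where it could mask a cortical difference or imitate one. Enrolling more patients would not reduce it.

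**Working it through.** The article states no figure on this point, so there is none to reproduce. The check is algebra, confirmed by simulation.

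**Inputs from the article:** separations of 8 mm and 3 cm; sampling at 3.9 Hz; 72 s blocks with 10 s intervals in the order 0-, 1-, 0-, 2-back (one block every 82 s); subtraction as the only scalp operation named.

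**Assumed, because the article gives no values:** k from 0.5 to 1.5; true cortical beta C = 1 in both groups; task-evoked scalp response S = 0.5 (COVID−) and 0.3 (COVID+).

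**Step 1, residue.** Long channel = C + k·S; short channel = S. Unscaled subtraction gives

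beta = C + k·S − S = C + (k − 1)·S.

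The scalp part cancels only at k = 1. With no correction the scalp part is k·S, so for k below 0.5 subtraction leaves more scalp signal, with the sign reversed, than doing nothing.

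**Step 2, group contrast.** With equal C,

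false difference (COVID+ minus COVID−) = (k − 1) × (0.3 − 0.5) = −0.2 × (k − 1).

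**Step 3, simulation.** The 1-back and 2-back blocks were the task, with the timing above and 300 replicates per cell. The short channel had little noise of its own (SD 0.09, against 0.3 in the long channel). Three corrections were compared: unscaled subtraction; subtraction of a scalp component scaled by a prior fit that omits the task; and the short channel as a regressor in the task GLM.

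| k | Beta, COVID− (algebra) | Beta, COVID+ (algebra) | False difference (algebra) | Simulated: unscaled | Simulated: prior fit | Simulated: GLM regressor |
|---|---|---|---|---|---|---|
| 0.5 | 0.75 | 0.85 | +0.10 | +0.08 | +0.06 | 0.00 |
| 0.75 | 0.875 | 0.925 | +0.05 | +0.05 | +0.05 | 0.00 |
| 1.0 | 1.00 | 1.00 | 0 | 0.00 | +0.06 | 0.00 |
| 1.25 | 1.125 | 1.075 | −0.05 | −0.04 | +0.06 | 0.00 |
| 1.5 | 1.25 | 1.15 | −0.10 | −0.12 | +0.06 | −0.01 |

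The mean beta with the GLM regressor was 1.00 to 1.01 in both groups. Repeat simulations on the same block timing gave the same pattern for unscaled subtraction: +0.07 to +0.12 at k = 0.5, zero at k = 1, and −0.08 to −0.11 at k = 1.5. The prior-fit residue was less stable; one repeat put it at no more than about +0.01, with betas of 0.96 to 0.98 against a true 1. It arises because cortex and scalp share the task timing, so a fit that omits the task credits some cortical response to the scalp.

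**Step 4, limit of the regressor.** If the short channel carries noise of its own, its estimated weight shrinks to k·λ, where λ (below 1) is the share of true scalp signal in the short-channel variance once the task is accounted for. The residue is then k·(1 − λ)·S. Comparing sizes, |k − 1| is smaller than k·(1 − λ) when k lies between 1/(2 − λ) and 1/λ. So near k = 1 plain subtraction can do better than the regressor.

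**The case against.** The strongest objection is that the article never says the subtraction is one-to-one. What it subtracts is the scalp change captured by the short pairs, which could mean a component scaled by a fitted coefficient. The custom scripts that would settle this are not shown, and a condensed article may leave such a weight to the code. A reader might infer that the plan commits to a weight of 1 and rejects regression; the text does not support that. What remains is that subtraction is the only operation named, in a paragraph that is otherwise specific, and that the GLM in 4.1 lists no short-channel term. The fitted-then-subtracted reading does not clearly remove the problem either, since it left some residue in simulation, of a size that depends on the noise assumed.

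A second objection is that a group bias needs a task-evoked scalp response that differs by COVID status. The hypothesis concerns endothelial function, and the skin test in 3.2.6 is hand perfusion after cuff release. Nothing in the article says that scalp flow during an n-back task differs by group. A reader might infer that the study's own hypothesis implies such a difference; it only makes one plausible. This objection stands.

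Third, the regressor's advantage depends on a nearly clean short channel (step 4). This also stands and belongs among the costs of the change.

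**Conclusion.** The point holds conditionally and is moderate in weight. Taken as written, the correction leaves (k − 1) times the scalp response in the NVC beta, and neither the stated geometry nor anything else in the article makes k equal to 1. A bias in the COVID contrast requires three things together: unscaled subtraction, k different from 1, and a task-evoked scalp response that differs by group. None of the three is established. Under the assumed responses of 0.5 and 0.3 the false difference is between +0.10 and −0.10, on a cortical beta of 1, for k between 0.5 and 1.5.

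It would be wrong to conclude that every patient's beta is contaminated, that the contamination is known to differ by COVID status, or that it masks rather than imitates an NVC deficit. The sign depends on k, which is not given. The point is still worth acting on because this beta carries the primary analysis in 4.1 and enters the primary dementia model in 4.2.

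**What to change.** Replace the subtraction sentence in section 3.2.2 with: *Short-channel signals are entered as nuisance regressors, with channel-specific estimated weights, in the first-level GLM together with the n-back block regressors; no direct subtraction is made.* Name the short-channel term in the first-level model of section 4.1 as well. Report the task-evoked short-channel beta by COVID group as a check: it shows directly whether the scalp response differs between groups, which is the condition that cannot be judged now. If the scripts already estimate the weights inside the GLM, only the sentence needs correcting.

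The cost is a few lines of script and a few degrees of freedom per channel. No new data are needed, and stored recordings can be reprocessed. Some scalp signal will remain if the short channels are noisy.
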